### Endpoints

The primary endpoint is the incidence of postoperative complications (Clavien–Dindo classification grade ≥ III) [35]. The rate of severe postoperative complications in all eligible patients will be investigated, and risk factors affecting them will be determined.

A key secondary endpoint is the incidence of intraoperative vascular injury around the SMV. The rate of intraoperative vascular injury around the surgical trunk in all eligible patients will be investigated, and risk factors affecting it will be extracted.

Other secondary endpoints include the incidence of postoperative complications (Clavien–Dindo classification grade ≥ II), 5-year overall survival, recurrence-free survival, and other short- and long-term outcomes (operative time, blood loss, conversion rate, degree of lymph node dissection, intraoperative complication rate, reoperation rate, R0 resection rate, local recurrence rate in the whole cohort and by stage, and incidence of bowel obstruction and herniated abdominal wall scarring). Factors influencing the above endpoints will be determined for all eligible patients. Furthermore, comparisons will be made between each subgroup, as shown in Table 1.

**Table 1 Tab1:** Secondary endpoints

1. Short-term results by approach (a. Medial approach vs. retroperitoneal approach; b. Medial approach vs. cranial approach; c. Retroperitoneal approach vs. cranial approach; a–c for laparoscopic surgery and robotic surgery, respectively)
2. Short-term results of robot-assisted and laparoscopic surgery (Comparison in all approaches, medial approach, retroperitoneal approach, and in each ASA-PS, respectively)
3. Short-term results by degree of lymph node dissection (D2, D3v, D3a)
4. Long-term results by approach, robot or laparoscopy, and degree of dissection
5. Impact of experience on short-term and long-term outcomes after the surgery performed by the surgeons before obtaining board certification in gastrointestinal surgery (including the investigation by each approach, robot/laparoscopy, and degree of lymph node dissection)
6. Impact of surgeons’ case volume prior to obtaining board certification in gastrointestinal surgery on short- and long-term outcomes following robot-assisted procedures
7. Impact of the participation of Endoscopic Surgical Skill Qualification-certified surgeons in surgery and their role in the procedure on short- and long-term outcomes
8. Impact of anastomosis method on short- and long-term outcomes

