Participating institution backgroundInstitution type and sizePatient backgroundPatient age; sex; body mass index; American Society of Anesthesiologists Physical Status; Eastern Cooperative Oncology Group performance status; albumin level; lymphocyte count; presence of dementia, diabetes, chronic kidney disease, chronic liver disease, or respiratory comorbidities; history of cardiac or cerebrovascular disease; use of steroids/immunomodulators and antithrombotic drugs; preoperative bowel obstruction; preoperative anaemia; abscess or peritonitis; preoperative therapy; history of laparotomy; timing of surgery; primary tumour location; and tumour stage at initial diagnosis (clinical stage, T factor, N factor).Technique and surgeonsWhether the surgeon is a board-certified gastrointestinal surgeon, whether an Endoscopic Surgical Skill Qualification-certified surgeon participates in the operation and his or her role, the approach, blood vessels to be dissected, procedure of dissecting the accessory right colic vein (via the cranial or caudal side), level and direction of lymph node dissection, instruments used during node dissection, method of anastomosis, combined resection of other organs, whether a robot is used, number of previous robotic-assisted right-sided colon resections (ileal resection, right hemicolectomy, or extended right hemicolectomy), and whether a robotic surgery proctor participates in the surgery if robotic surgery is used.Surgical outcomesThe date of surgery, operation time, blood loss, presence of intraoperative vascular injury, other intraoperative complications, 30-day postoperative survival, open conversion, intraoperative blood transfusion, details and grade of postoperative complications within 30 days (Clavien–Dindo classification grade ≥ II), onset and date of intervention for cases with anastomotic leakage/deep wound infection (surgical site infection [SSI]), enforcement and date of reoperation, drain placement, anti-adhesive placement, date of discharge, and operative death.In cases of intraoperative vascular injury:Timing of intraoperative vascular injury; response to intraoperative vascular injury; unplanned bowel resection due to bleeding; open conversion due to bleeding; final post-haemostatic status; and amount of blood transfusion, blood products, and albumin administered from intraoperative to postoperative day 3.Surgical deathsCause of death, date of death, and date of therapeutic intervention.Pathological and histological findings and postoperative courseTumour diameter, histological type (main), pathological stage, T-factor, N-factor, R-status, number of harvested lymph nodes, number of lymph node metastases, presence and details of adjuvant therapy, survival outcome, date of confirmation of final survival outcome, date of confirmation of recurrence, and type of initial recurrence.Patients with pStage 0 and pStage IV will be censored, and no follow-up will be performed after initial postoperative discharge. The development of intestinal obstruction (Clavien–Dindo classification grade ≥ II) and abdominal wall scar hernia will be investigated during follow-up. Patients will be followed up during the postoperative period according to the Japanese Society for Cancer of the Colon and Rectum guideline schedule, and tumour marker levels, thoracoabdominal computed tomography (CT) results, and colonoscopy results will be collected. Omitting observations as part of routine medical care will be deemed acceptable at the discretion of the treating physician [36].

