Secondary endpoints: Summary statistics for patient background and other surgical outcomes will be calculated. A multivariate logistic regression or multiple regression analysis will be performed using the factors listed in the survey items that may influence outcomes. A random-effects model will be used to account for differences between the centres. The main endpoint for short-term outcomes for each subgroup is postoperative complications (Clavien–Dindo classification grade ≥ II), and group comparisons will be conducted after propensity score matching (differences between groups will be tested using Student’s t-test and the χ^2^ test) and logistic regression to identify confounders. Multiple regression analysis will be used to analyse continuous variables. A random-effects model will be used to account for the differences between institutions. The Kaplan–Meier method will be used to plot cumulative late complication curves, local and overall recurrence-free survival curves, and overall survival curves for long-term outcomes. To account for confounding factors, a multivariate Cox regression analysis will be performed using preoperative and postoperative factors that may contribute to recurrence and late complications, and risk factors will be examined. In addition to regression analysis of factors, each factor will be discussed from clinical and medical perspectives to reach a combined perspective.

The number of experienced cases will be added to the factors in the multivariate analysis to examine their effect on the outcome. The correlation of the number of cases experienced and outcomes (operation time and blood loss) with the learning curve will be evaluated using the moving average method and the cumulative sum curve.

Statistical significance will be set at *p* < 0.05.

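### Analyses of surgeon attributes name the institution as the only random-effect level, which understates their standard errors if surgeons differ within a site

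*Protocol article*

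**What the plan says.** The Statistical analysis section names a random-effects model three times, always at one level:

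- primary and key secondary endpoints: "A random-effects model will be used to account for the differences between institutions";
- secondary endpoints: "A random-effects model will be used to account for differences between the centres";
- subgroup comparisons and continuous outcomes: "Multiple regression analysis will be used to analyse continuous variables. A random-effects model will be used to account for the differences between institutions".

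Several planned analyses concern the operator. In the Endpoints section, Table 1 item 5 covers operations by surgeons not yet board certified. Item 6 is "Impact of surgeons’ case volume prior to obtaining board certification in gastrointestinal surgery on short- and long-term outcomes following robot-assisted procedures". Item 7 is "Impact of the participation of Endoscopic Surgical Skill Qualification-certified surgeons in surgery and their role in the procedure on short- and long-term outcomes". The Statistical analysis section adds "The number of experienced cases will be added to the factors in the multivariate analysis to examine their effect on the outcome", with significance at p < 0.05. It then says that the relation of case number to operation time and blood loss "will be evaluated using the moving average method and the cumulative sum curve".

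Among the technique and surgeon items, Observation, investigation data, and methods lists certification, role and "number of previous robotic-assisted right-sided colon resections". It lists no operator code.

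**The concern.** Cases done by one surgeon share that surgeon's speed and skill. Certification and prior volume are fixed, or nearly fixed, for a given surgeon, so the information on them comes largely from comparing surgeons. An institution intercept removes differences between hospitals but not differences between surgeons in the same hospital. The model then treats repeated cases by one surgeon as more independent than they are.

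The article's own reasoning makes surgeon variation plausible. The Background suggests that surgeon proficiency may matter for safety, while the Discussion argues that institutional experience will not affect the outcomes. The plan therefore models the level it expects to matter less and leaves out the one that these analyses study.

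At stake are the conclusions on whether uncertified or low-volume operators take longer or lose more blood and, to a lesser degree, whether they have more complications. The learning curve raises a separate issue. If case number is plotted across surgeons, a downward trend may only show that surgeons with high counts differ from those with low counts.

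**Working it through.** **From the article.** 2,000 cases and 73 facilities give 2,000/73 = 27.4 cases per facility. The test level is 0.05, taken as two-sided. The institution is the only random-effect level.

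**Assumed, because the article gives no figure.** Surgeons per institution 2 to 9; surgeon ICC ρ from 0 to 0.15; institution ICC 0.05; event rate 10% for the binary outcome.

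**The plan's own figure.** The normal-approximation sample size is 1.96² × 0.05 × 0.95 / 0.01² = 1,825. The exact binomial interval reaches an average half-width of 1.0 point from about n = 1,940, and at n = 2,000 it runs from 4.09% to 6.05%. The target of about 2,000 is reproduced and does not depend on this point.

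**Approximate formula.** For a factor constant within surgeon, with m cases each, the true variance is about 1 + (m − 1)ρ times the one used. The actual level is then 2{1 − Φ(1.96/√(1 + (m − 1)ρ))}.

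- m = 14, ρ = 0.05: 1 + 13 × 0.05 = 1.65; √1.65 = 1.28; 1.96/1.28 = 1.53; level 12.7%.
- m = 9, ρ = 0.10: 1 + 8 × 0.10 = 1.80; √1.80 = 1.34; 1.96/1.34 = 1.46; level 14.4%.
- m = 3, ρ = 0.05: 1 + 2 × 0.05 = 1.10; √1.10 = 1.05; 1.96/1.05 = 1.87; level 6.2%.

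**Simulation, continuous outcome.** 73 institutions, 2,000 cases, a binary surgeon-level factor with no true effect, an institution intercept only, 1,500 runs per cell. The Monte Carlo standard error near 5% is √(0.05 × 0.95/1,500) = 0.6 points.

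| Surgeons per site (cases each) | ρ = 0.02 | 0.05 | 0.10 | 0.15 |
|---|---|---|---|---|
| 2 (13.7) | 7.3% | 13.1% | 18.8% | 26.7% |
| 3 (9.1) | 6.7% | 8.6% | 13.7% | 19.1% |
| 5 (5.5) | 6.3% | 6.3% | 9.9% | 14.5% |
| 9 (3.0) | 5.1% | 7.6% | 7.8% | 7.9% |

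With ρ = 0 the level is 4.1–5.3%, so the excess comes from the surgeon effect. Adding a surgeon level brings it to 4.0–5.9% in all 20 cells (the 16 above and the four with ρ = 0).

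**Factor that also varies within surgeon.** If half its variance lies within surgeon, as with a growing case count, the level is 7.3% instead of 13.7% (3 surgeons, ρ = 0.10).

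**Simulation, binary outcome at 10%.** Logistic mixed model, likelihood-ratio test, 600 runs per cell; Monte Carlo standard error near 5% is √(0.05 × 0.95/600) = 0.9 points.

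| Surgeons per site | latent ρ = 0.05 | 0.10 | 0.15 |
|---|---|---|---|
| 2 | 5.7% | 9.5% | 13.2% |
| 3 | 4.7% | 7.0% | 10.0% |
| 5 | 5.0% | 5.8% | 6.8% |

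**Learning curves.** No clustering level and no significance test is stated for the moving average or the cumulative sum, so no error rate applies to them. What can be said is that a curve over pooled cases does not separate differences between surgeons from change within a surgeon.

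**The case against.** The strongest objection is that the main short-term endpoint for the subgroups is binary (complications of grade II or higher). At an assumed 10% rate and latent ICC 0.05, the simulated levels of 4.7–5.7% cannot be told apart from 5%. This stands: a reader might infer that every surgeon-level test runs above its nominal level, and the documents do not support that.

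Three further limits also stand.

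- Prior case number is listed only for robotic operations. The Discussion expects nearly equal robotic and laparoscopic numbers, so the experience analysis has about 27.4/2 = 13.7 cases per site. With 2 surgeons of 7 cases each, a simulated experience count gave 7.5% at ICC 0.05 and 12.2% at 0.10, below the largest figures above.
- Table 1 item 7 is partly a team attribute of the case. Under Definition of assessment data, item 12, the qualified surgeon may be assistant, scope operator or consultant. The point applies to item 7 only where that surgeon is the operator.
- Item 10 of the same section allows partial operators, so surgeon is not a perfectly clean level.

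A reader might also infer from the data list that cases cannot be linked to a surgeon. That does not follow. The article is condensed and lists no institution code either, although institution effects are planned. Nor do the documents support a false-positive rate for the learning curve, since no test of it is stated.

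The full protocol or analysis plan, not shown, might add a surgeon term. But the article is not silent on clustering: it states the level each time, and for operator attributes that level is incomplete.

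**Conclusion.** The point holds in conditional form. If surgeons differ within institutions and contribute several cases each, the institution-only models give standard errors that are too small for operator attributes. For a continuous outcome and a purely surgeon-level factor, the type I error is about 6–13% at ICC 0.05 and 8–19% at 0.10, assuming 2 to 9 surgeons per site. It is lower when the factor also changes within surgeon. For a complication at about 10%, with 2 to 5 surgeons per site, it is about 5–6% and 6–10%. All of this rests on assumed ICCs, caseloads and event rate. Only secondary analyses are at issue; the target of 2,000 cases is not. The learning curves need a separate statement of how surgeons are handled.

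**What to change.** In the models for Table 1 items 5 to 7 and for number of experienced cases, state random intercepts for institution and for main operator nested in institution, with operator-clustered standard errors if that model does not converge. Draw the moving-average and cumulative-sum curves within surgeon, or on residuals from that model. Confirm that the Electronic Data Capture system holds an operator code. If it does not, add an anonymised one, back-filled from operation records, with a rule for cases shared between operators. Splitting experience into between-surgeon and within-surgeon terms is optional.

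The cost is at most one coded field for each of about 2,000 cases and one more variance term in models already planned with random effects. Intervals for surgeon-level effects widen: by the formula above, about 1.05 times at 3 cases per surgeon and 1.28 times at 14, with ICC 0.05. No extra patients or procedures are needed. Enrolment runs to 31 May 2026 and the short-term analysis starts at the earliest 120 days after enrolment ends, so there is time to do this before it is needed.

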## Discussion

Successfully performing surgical procedures without intra- or postoperative complications is critical. A national survey in Japan demonstrated that the mortality rate of right hemicolectomy was higher than that of low anterior resection [7]. However, no detailed studies regarding the factors influencing the safety of this procedure have been conducted. Therefore, we will conduct the SCaRLET study to identify the rate and cause of severe perioperative complications in laparoscopic right-sided colectomy.

To the best of our knowledge, this will be the first large prospective study of laparoscopic right-sided colectomy in Japan, with nearly equal numbers of laparoscopic and robotic procedures. This study is characterised by a low event selection bias owing to its prospective nature. It will be conducted at Japanese institutions that excel in JSLCS, with high proficiency levels of performing laparoscopic and robotic surgeries. Hence, the institutional experience will not affect the study outcomes, potentially determining the actual safety of the procedure. We will investigate the actual incidence and causes of high mortality rates due to the procedure, which have not yet been clarified. Furthermore, we will investigate the actual incidence and causes of intraoperative vascular injury, which may be the only critical aspect in D3 lymph node dissection.

A major operational challenge is the difficulty of case accumulation inherent in large-scale prospective registration. Although more than 70 institutions are participating nationwide, the success of the study depends on their consistent and proactive cooperation. Timely and accurate data entry, strict protocol adherence, and sustained engagement throughout the study period require substantial coordination. Although not addressed in other sections, these logistical demands are essential to the feasibility and execution of the study. Several strategies may be considered to address this operational challenge. Firstly, obtaining informed consent via the opt-out method, in accordance with the guidelines of the Regional Bureau of Health and Welfare, simplifies the consent process and may substantially lower the barrier to patient enrolment. This procedural efficiency is particularly beneficial in busy clinical settings, where it can contribute to improved recruitment rates. Secondly, sustained engagement of participating institutions may be promoted through regular progress updates and personalised communication. Periodic email distributions, online meetings, and study group sessions that emphasise the scientific significance and clinical relevance of the research may foster a sense of ownership and motivation among site investigators. Fortunately, the study topic currently attracts considerable attention nationwide, and continued outreach efforts will be made to maintain interest. Thirdly, detailed centralised support provided by the study office—such as a coordinating centre or help desk—can assist institutions with protocol compliance, data entry, and technical troubleshooting. This support system not only enhances data quality but also alleviates administrative burden at each site. Lastly, clearly recognising institutional contributions through authorship opportunities is expected to encourage active participation and reinforce accountability. In addition to the primary analysis, numerous secondary analysis themes are planned, thereby increasing opportunities for authorship. Investigators who meet authorship criteria will be credited as part of a group collaborative. Collectively, these measures are expected to mitigate logistical barriers and enhance the feasibility and execution of large-scale prospective studies.

Another concern is that cases with poor general condition may be excluded or that surgeons may adopt more conservative approaches to prioritise safety, potentially reducing the observed complication rates. And it is essential that all eligible cases be registered without modification, and that surgical procedures be performed strictly in accordance with routine clinical practice, without deviation. To ensure the validity and generalizability of the study findings, comprehensive data collection on patient demographics, surgical techniques, and perioperative variables is planned, thereby enabling precise interpretation of the clinical and procedural contexts in which the outcomes are generated.

Given the absence of prior nationwide studies, the SCaRLET study holds significant value not only within Japan but also in the broader global context. As a multicentre, prospective investigation conducted under standardised conditions across high-performing institutions, it may serve as a landmark for best practices domestically and globally. The findings have the potential to contribute to international surgical literature and guide the evolution of safe and effective approaches to right-sided colectomy worldwide.

In conclusion, this large-scale, nationwide, multicentre, prospective study aims to identify key factors affecting the safety of laparoscopic right-sided colectomy. The findings will provide actionable insights to enhance surgical safety and inform best practices in colorectal surgery across Japan and worldwide.

## Data Availability

The datasets used and/or analysed during the current study will be available from the corresponding author on reasonable request.

## Abbreviations

CME: Complete mesenteric excision
CT: Computed tomography
CVL: Central vascular ligation
ESSQS: Endoscopic Surgical Skill Qualification System
IVR: Interventional radiology
JSLCS: Japan Society of Laparoscopic Colorectal Surgery
MCA: Middle colic artery
RCT: Randomised controlled trial
SMA: Superior mesenteric artery
SMV: Superior mesenteric vein
SSI: Surgical site infection
TAPP: Transabdominal preperitoneal
